### Proposed analytic strategy

#### Sample description

The number of participants completing the 12 exercise courses and each of the assessment waves will be tabulated. The number of participants withdrawing during the course of the study will be tabulated by reason for withdrawal where known. The data will be screened to detect outliers and assess the distributions of the primary and secondary outcome variables. Outliers will not be excluded from analyses unless there is independent evidence that their scores are not valid.

Demographic and other patient characteristics (age, sex, weight, height and BMI) recorded on screening will be tabulated by treatment arm. Descriptive statistics will include n, mean, standard deviation, median, minimum and maximum. Differences in baseline levels of outcome variables (activity, BMI, and so forth) will be identified.

#### Intervention effectiveness

For the primary outcome of activity, and assuming normal variable distributions, the intervention arms will be compared to the control arm using *t*-tests and one-way analysis of covariance using study arm as the between-subjects factor and baseline activity scores as the covariate (following Senn,
[36]). Similar analyses will be conducted for the secondary outcome variables and in all cases effect sizes reported. Where variable distributions do not initially permit the use of parametric inference tests, variables will be subjected to mathematical transformation to achieve normality. In cases where transformations are not effective, non-parametric tests on difference scores will be used. Differences between arms in the proportions achieving more than 10 mmHg reductions in blood pressure will be assessed using chi-square tests.

Analyses will be conducted on a per-protocol basis. Interim assessment of the efficacy of the interventions will be made at 6 months.

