### Sample size and power calculations and randomisation

Davies and colleagues report a meta-analysis of internet-based exercise intervention studies which suggests an average effect size of d = 0.14
[16]. A Cochrane review of general interventions to promote activity among inactive adults reports an average SMD = 0.28, but notes considerable heterogeneity in effects sizes
[4]. In the case of internet interventions aimed at reducing blood pressure, effects sizes of the order of SMD = 0.27 and 0.17 for systolic and diastolic blood pressure, respectively (equating to drops of 3.8 and 2.1 mmHg, respectively), have been identified in a recent meta-analysis
[35]. Based on these analyses, an effect size of 0.125 can be assumed for comparing means of MET-minutes per week and mmHg between the intervention and control arms (equinumerous) for a two-arm study. With this effect size, if each arm consists of 500 subjects, a power of 80% is obtained for a two-sided statistical contrast to show statistical significance, at the 5% level, of the difference of the means of the two arms with respect to these outcome variables. It is therefore decided that there will be 500 subjects in each of the four arms of the present study.

Block randomisation is to be conducted by the University of Surrey’s Clinical Research Centre. Participants cannot be blinded to the nature of the intervention they are receiving and for reasons of monitoring and contacting participants the research assistant also cannot be blinded. The primary analyst will be blinded to participant allocation.

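### Two analyses, t-tests and baseline-adjusted ANCOVA, are named for the primary outcome, with neither primary and no rule if they disagree

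*Protocol article*

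**What the plan says.** Under Intervention effectiveness, the article states that for the primary outcome "the intervention arms will be compared to the control arm using" t-tests and a one-way ANCOVA, with study arm as the factor and baseline activity as the covariate. A methodological source is cited for the ANCOVA. Neither analysis is called primary and no order is given. The same section adds: "Interim assessment of the efficacy of the interventions will be made at 6 months". It attaches no test, significance level or decision rule to that assessment.

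The abstract fixes the primary outcome as MET-minutes per week by IPAQ at 1 year. Methods/design lists one control arm (gym referral, GPGR) and three intervention arms (GPGR + WEB, SPR, SPR + WEB).

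The only significance level in the article is in the sample size section, for a "two-sided statistical contrast to show statistical significance, at the 5% level, of the difference of the means of the two arms". That calculation is framed as a comparison "between the intervention and control arms (equinumerous) for a two-arm study", and its result is then applied to four arms: "It is therefore decided that there will be 500 subjects in each of the four arms of the present study".

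**The concern.** An unadjusted t-test and a baseline-adjusted ANCOVA of the same outcome estimate the same effect but give different p-values. When both are named and neither is ranked, following the plan literally produces two answers for every intervention-versus-control contrast. If one is significant and the other is not, nothing settles which result the trial reports. A claim made on whichever test succeeds has a false-positive rate above the nominal level.

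The two analyses also differ in precision. Baseline activity is collected anyway, and the t-test makes no use of it.

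A secondary matter is that the 5% level was set for one contrast of two arms, while the trial has three contrasts sharing one control. The article does not say whether 5% is meant per contrast or across the three.

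**Working it through.** **Inputs from the article.** Effect size d = 0.125; 500 per arm; two-sided 5% for one contrast; stated power 80%; three intervention arms against one control.

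**Assumed.** The correlation r between baseline and 12-month activity is not given; the range 0.3 to 0.7 is used. The t-test is taken to be on the 12-month score, because the article does not say which score it uses.

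**1. The plan's own power figure.** For an unadjusted comparison the expected z is d × √(n/2) = 0.125 × √250 = 1.976. Power = Φ(1.976 − 1.960) = 50.7%. The stated 80% is not reproduced. It would fit a pooled 1,000 v 1,000 comparison (79.8%) or ANCOVA with r of about 0.71 (80.1%), but the article states neither. That is a separate issue; the 51% is needed here only as the t-test benchmark.

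**2. Power by ANCOVA.** Adjustment multiplies the residual variance by 1 − r², so the expected z becomes 1.976/√(1 − r²).

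| r | expected z | power by ANCOVA | gain over t-test (points) |
|---|---|---|---|
| 0.3 | 2.072 | 54.5% | 3.8 |
| 0.5 | 2.282 | 62.6% | 12.0 |
| 0.7 | 2.768 | 79.0% | 28.4 |

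The gain is also a floor on how often the two tests disagree at d = 0.125, because P(ANCOVA significant and t-test not) is at least the difference between the two powers.

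**3. False positives for one contrast if either test may count.** Under the null the two z statistics have correlation √(1 − r²): 0.954, 0.866 and 0.714 for r = 0.3, 0.5 and 0.7. With each test at |z| > 1.96, simulation (1,000,000 runs) gives the chance that at least one is significant:

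- r = 0.3: 6.4%
- r = 0.5: 7.3%
- r = 0.7: 8.3%

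The excess over 5% is therefore 1.4 to 3.3 points. The chance that exactly one test is significant is 2 × (either) − 10%, which is 2.8% at r = 0.3 and 6.6% at r = 0.7.

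If the t-test were on change scores, the correlation between the statistics would be √((1 + r)/2), or 0.81 to 0.92. That lies inside the 0.71 to 0.95 above, so the false-positive rate stays within the same 6.4% to 8.3%. ANCOVA also remains the more precise analysis, since 1 − r² = (1 − r)(1 + r) ≤ 2(1 − r).

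**4. Three contrasts against a shared control.** With equal arms the contrasts have pairwise correlation 0.5. If each is tested by one method at two-sided 5%, the exact familywise error is 12.5% (14.3% if they were independent). Dunnett control at 5% needs a critical z of 2.349, or 0.0188 two-sided per contrast. Per-contrast power by t-test becomes Φ(1.976 − 2.349) = 35.5%. By ANCOVA it is Φ(2.072 − 2.349) = 39%, Φ(2.282 − 2.349) = 47% and Φ(2.768 − 2.349) = 66% for r = 0.3, 0.5 and 0.7.

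**The case against.** **The unseen plan may settle it.** An article condenses a fuller document, and a statistical analysis plan could rank the analyses and set a multiplicity rule. For the multiplicity rule this stands: silence is not evidence that none exists. It does not remove the main point. The article does not leave the primary analysis open; it names two, and a later plan that chose one would be changing what is published.

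**The ANCOVA may be an omnibus test.** It could be read as one test across four arms, with the t-tests as the pairwise follow-up. The either-test figures would then not apply as they stand. But the article gives no such sequence, and a baseline-adjusted overall test followed by unadjusted pairwise tests could still conflict without a rule.

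**Per-contrast 5% is defensible.** Research questions and hypotheses judges the interventions individually, so familywise control is a choice. This stands; the plan need only say which is meant.

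**Method choice alone adds little.** The inflation is 1.4 to 3.3 points per contrast. This also stands. The missing rule for a split result and the loss of precision carry more weight.

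**Stronger readings that the article does not support.** A reader might infer that everything is tested at an unadjusted 5%, so that the trial's error rate is misstated. The article gives 5% for one two-arm contrast, sets no level in the analysis section, and nowhere presents 5% as a trial-wide rate. A reader might also count the 6-month assessment as a second chance at success, giving up to 12 tests (3 contrasts × 2 methods × 2 times) and a much larger error. The primary outcome is at 1 year, and no rule lets a 6-month result count as success or stop the trial.

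**Conclusion.** The point holds in limited form and should be corrected. The article fixes two analyses of one primary outcome and ranks neither. If either may support a claim at two-sided 5%, the error for a single contrast is about 6.4% to 8.3%. This rests on an assumed baseline correlation of 0.3 to 0.7 and on ANCOVA supplying the pairwise contrast. Relying on the t-test gives about 51% power, against about 54% to 79% by ANCOVA over the same range.

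The 12.5% familywise figure needs no baseline correlation, but it holds only if each of the three contrasts is tested at 5%. It is a reason to state what the 5% refers to, not evidence that the plan breaches a level it set.

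**What to change.** - Name baseline-adjusted ANCOVA of 12-month IPAQ MET-minutes per week, with the three intervention-versus-GPGR contrasts, as the sole primary analysis. Drop the t-tests or label them supportive. This is a wording change; it needs no new data and gains precision from the baseline already collected.
- Label the 6-month efficacy assessment secondary, so that it cannot support a primary claim. This has no cost.
- State whether 5% is per contrast or familywise. Keeping it per contrast costs nothing but should be declared. If familywise, use Dunnett for the three contrasts; at d = 0.125 and 500 per arm this lowers per-contrast power from about 51% to about 35% on the t-test scale, and from about 54%–79% to about 39%–66% by ANCOVA for r of 0.3 to 0.7.

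The planned arm-versus-control contrasts should stay. Replacing them with pooled factorial main effects would change the question, since the article asks about the interventions separately and in combination.

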## Abstract

**Background:**

Increasing physical activity is known to have health benefits for people with hypertension and related conditions. Current general practitioner referrals for gym-based exercise increase physical activity but meta-analyses show that while these are effective the absolute health risk reduction is small due to patients failing to maintain activity levels over time. This study assesses the effectiveness of two sports-oriented interventions that are intended to bridge the intention-behaviour gap and thus increase the likelihood of sustained increases in physical activity.

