**Methods/design:**

Four-arm randomised controlled trial. The study tests two types of intervention that are intended to increase physical activity among currently inactive 18- to 74-year-old people with hypertension or high-normal blood pressure. This study will assess the effectiveness of a 12-week sports-oriented exercise programme, the efficacy of a web-delivered self-help tool to promote and support sports participation and healthy behaviour change and the effect of these interventions in combination. The control arm will be a standard care general practitioner referral for gym-based exercise. Participants will be allocated using block randomisation. The first author and primary analyst is blinded to participant allocation. The primary outcome measures will be time spent in physical activity assessed in metabolic equivalent minutes per week using the International Physical Activity Questionnaire 1 year after commencement of the intervention. Secondary outcomes include increased involvement in sporting activity and biomedical health outcomes including change in body mass index, and waist and hip measurement and reductions in blood pressure.

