## Methods/design

Participants will be inactive people aged 18 to 74 years who are eligible to be referred by their GPs for an exercise intervention. Participants will be people with hypertension or high-normal blood pressure and assessed as being inactive or moderately inactive using the General Practice Physical Activity Questionnaire (GPPAQ) screening tool. The inclusion and exclusion criteria are detailed below.

The study will be conducted in the Guildford and Waverley CCG area (Surrey, UK) and patients will be recruited via GP surgeries serving catchment areas within reasonable reach of Surrey Sports Park and the five DC leisure centres in Waverley, Surrey, UK. We have designed the study with the intention to allow recruitment for all patients eligible for an exercise referral within the 9 months of the proposed trial data collection phase.

The trial design is shown in Figure 1. The key features are that, after a patient has been assessed as likely to benefit from an exercise intervention, their referral is to the project research assistant who will allocate the patient to one of four conditions on the basis of previous independent randomisation. These are: 1) GP gym-based referral (GPGR, the treatment as usual control); 2) GP gym-based referral plus web tool (GPGR + WEB); 3) sport referral at Surrey Sports Park (SPR); and 4) sport referral at Surrey Sports Park plus web tool (SPR + WEB). After obtaining informed consent patients attend a 12-week exercise programme (sport or gym) and their activity levels and sporting participation are monitored again at 6 months and 12 months after starting the exercise programme. Pending ethical approval the intention is to commence recruitment in the early autumn of 2013 for a period of 9 months.

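### The 12-month t-test/ANCOVA makes no use of the 6-month activity score, so the primary contrast can be biased, in either direction, if activity-related drop-out differs by arm

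*Protocol article*

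**What the plan says.** The abstract (Methods/design) defines the primary outcome as "time spent in physical activity assessed in metabolic equivalent minutes per week using the International Physical Activity Questionnaire 1 year after commencement of the intervention". Under Intervention effectiveness, the arms are compared with control by t-tests and by "one-way analysis of covariance using study arm as the between-subjects factor and baseline activity scores as the covariate". So the adjusted model uses two scores per person: baseline and 12 months.

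Methods/design adds an intermediate wave: "their activity levels and sporting participation are monitored again at 6 months and 12 months after starting the exercise programme". Its only stated role in the analysis is under Intervention effectiveness: "Interim assessment of the efficacy of the interventions will be made at 6 months".

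On losses, Sample description says: "The number of participants withdrawing during the course of the study will be tabulated by reason for withdrawal where known". The one statement about who is analysed is "Analyses will be conducted on a per-protocol basis". The article gives no expected drop-out rate.

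**The concern.** A t-test or ANCOVA of the 12-month score needs a 12-month score. Someone who answered at baseline and 6 months and then fell silent drops out of the contrast, although the 6-month answer is likely to be a good predictor of the missing value.

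The trial exists because exercise referral is weakened by "patients failing to maintain activity levels over time". If people who have lapsed by 6 months are less likely to answer at 12 months, the responders in each arm are more active than the arm as a whole. When that selection is stronger in one arm, part of the observed difference reflects who answered. The planned effect is only 0.125 SD, so modest selection could hide a real difference or produce a false one.

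**Working it through.** **The plan's own figure.** The article states no figure for drop-out. Its yardstick is the planned effect of 0.125 SD with 500 per arm and 80% power at two-sided 5%. Check: 0.125 × √(500/2) = 1.976; 1.976 − 1.960 = 0.016; power = Φ(0.016) = 50.7%, not 80% (80% needs about 1,005 per arm). That is a separate point. Here 0.125 serves only as the scale for bias.

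**Assumed inputs (none is in the article).** Scores are normal with SD 1. Correlations are baseline/6-month 0.4, baseline/12-month 0.4 and 6/12-month 0.6. The true effect is 0.125 at both follow-ups. Where drop-out is selective, its log-odds fall by 1 per SD of the 6-month score.

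**Approximate bias by formula.** Let S be the amount by which responders' mean 6-month score exceeds that of their whole arm. Given baseline, the responders' 12-month mean in that arm is then too high by about

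S × (r6,12 − r0,6 × r0,12) = S × (0.6 − 0.4 × 0.4) = 0.44 × S.

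The bias of the contrast is 0.44 × (S intervention − S control). Integrating the logistic drop-out curve over a standard normal gives S = 0.173, 0.253 and 0.332 for 20%, 30% and 40% loss, and S = 0 for random loss.

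- Same mechanism, 30% in both arms: 0.44 × (0.253 − 0.253) = 0.
- 30% control, 20% intervention: 0.44 × (0.173 − 0.253) = −0.035.
- 40% control, 20% intervention: 0.44 × (0.173 − 0.332) = −0.070.
- 30% in both, selective in control only: 0.44 × (0 − 0.253) = −0.111.
- 30% in both, selective in intervention only: +0.111.

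**Simulation, 1,000,000 per arm, true difference 0.125.**

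| Assumed 12-month loss | Formula | ANCOVA in responders | Estimate using 6-month score |
|---|---|---|---|
| 30% / 30%, random | 0.125 | 0.123 | 0.123 |
| 30% / 30%, same selection | 0.125 | 0.124 | 0.123 |
| 30% control / 20% intervention | 0.090 | 0.091 | 0.127 |
| 20% control / 30% intervention | 0.160 | 0.159 | 0.122 |
| 40% control / 20% intervention | 0.055 | 0.055 | 0.126 |
| 30% / 30%, selective in control only | 0.014 | 0.015 | 0.127 |
| 30% / 30%, selective in intervention only | 0.236 | 0.240 | 0.127 |

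Simulation error is about √(2/700,000) × √(1 − 0.4²) = 0.0015, so the first two rows show no bias.

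**Other assumptions, 500 per arm, 3,000 runs, correlations 0.5/0.5/0.6, about 30% missing, selection in control only.** The multiplier becomes 0.6 − 0.25 = 0.35. With slope 1, the formula gives 0.35 × 0.253 = 0.089, and simulation about 0.09. A milder slope of about 0.6 gives 0.06 SD: with no true effect, ANCOVA rejects in 15% of runs, against 5% for the repeated-measures estimate. With a true effect of 0.125, power is 17% against 48%.

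**Drop-out driven by the unseen 12-month score** (30% control, 20% intervention). ANCOVA gives 0.057 and the method using the 6-month score gives 0.072, against a truth of 0.125. The bias falls from 0.068 to 0.053, so only 0.015/0.068 = 22% of it is removed.

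**Precision under equal random loss.** At 30% loss the SE is 0.0641 for ANCOVA and 0.0627 for repeated measures (2% smaller). At 40% loss with a 6/12-month correlation of 0.7 it is 0.0718 against 0.0667 (7% smaller). With complete data both are 0.0554.

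**The case against.** **The plan does not say that non-responders are discarded.** This stands. The article names a test and a covariate and is silent on imputation, a matter that a condensed article commonly leaves to the full protocol or SAP. The silence is not the finding. The point is narrower: the model that is stated has no place for the 6-month score. ANCOVA is also compatible with imputation that uses that score, so a mixed model is not the only remedy.

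**Selective loss alone does not bias the contrast.** This stands too. A reader might infer that losing lapsed participants is enough; the second row of the table shows otherwise. The largest figures come from assuming full selection in one arm and none in the other, and the sign depends on which arm.

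**The documents do not show differential non-response.** Correct. The passages on failed maintenance concern lapse from activity, not unanswered questionnaires. A reader might point to the web arms' email and text prompts, but Interactive web tool describes these as activity reminders whose means and frequency the patient controls, not as follow-up chasers. Every participant must have internet and email. A difference between arms in contact makes unequal response possible; it is not evidence of it.

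**The 6-month score is not wholly ignored.** True: it serves the interim assessment. It is unused in the primary contrast.

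**The remedy looks perfect only because the simulation was built that way.** Largely true. Its near-zero bias follows from making drop-out depend on an observed score, and participants lost before 6 months still contribute no follow-up data.

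**Conclusion.** The point holds in a conditional form. The stated primary analysis leaves out a score that the trial already collects, and this exposes the 12-month contrast to bias if drop-out related to 6-month activity differs by arm. Under the assumptions shown, the bias runs from 0 (identical drop-out), through about 0.03 SD or a quarter of the planned effect (30% against 20% loss), to about 0.06–0.11 SD or roughly half to nine tenths of it (selection in one arm only). It can go in either direction. The correlations, loss rates and drop-out slopes are all assumptions.

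The documents do not support the stronger statement that the primary contrast is biased, nor the claim that using the 6-month score would make it unbiased whatever the cause of drop-out. This is a low-cost improvement worth making, not an error in a stated figure. The per-protocol basis is a related but separate matter.

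**What to change.** Make the primary analysis a linear mixed model for repeated measures of 6- and 12-month MET-minutes, transformed if needed. Include arm, time, arm-by-time, baseline, baseline-by-time and an unstructured covariance. Include every participant with at least one follow-up score, and keep the 12-month arm contrast as the primary estimate. The baseline-by-time term is needed for the model to match the planned ANCOVA when data are complete. ANCOVA after multiple imputation that uses the 6-month score is an acceptable equivalent.

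Add a missing-not-at-random sensitivity analysis, for example one that shifts the assumed 12-month values of non-responders by differing amounts in each arm. The per-protocol sentence must be reconciled with whichever analysis set is chosen.

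The cost is revised analysis wording and slightly more analysis work, with no new data. The analysis then relies on data being missing at random given baseline and 6-month scores. If loss proves equal and random, the gain is only about 2–7% in SE.

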### Measures

PA will be assessed via an online questionnaire using the short-form version of the International Physical Activity Questionnaire
[29], which is a well validated measure of physical activity in a number of domains and permits the calculation of MET per minute values for activities in each domain, including leisure and sporting activity
[30]. As recent research has shown that the International Physical Activity Questionnaire can overestimate activity in sedentary individuals we will use a second validated self-report measure, the Self-Report Walking and Exercise Tables
[31] that also permits the estimation of MET minutes. We will include additional items to tap the types of sporting activity people do.

Participants will complete the GPPAQ screening tool at the beginning and end of the study for inclusion on their patient records.

Health indicators will include measures of height and weight (body mass index (BMI)), waist and hip circumference, and blood pressure. These measures will be assessed by the exercise professional at the beginning, middle and end of the 12-week exercise programme. They will be collected again at the end of the 12-month period on visiting their GP surgery. Patients will be asked to consent to the collection of their most recent blood sugar, cholesterol/high-density lipoprotein ratio and indications of whether they are receiving treatment for high blood pressure. We will ask for access to medical records to assess whether they have chronic kidney disease, diabetes, rheumatoid arthritis or atrial fibrillation. These indicators are required for the QRisk2 calculations. To assess safety we will also monitor well-being during the period of the exercise programmes. Blood pressure measurements will be taken by the research team and/or by specially trained exercise professionals using Omron M6W blood pressure monitors (Omron Health Care Co. Ltd, [name]).

General health will be assessed with the RAND SF36
[32] along with short measures of drinking (the AUDIT
[33]) and smoking behaviour (The Fagerstrom Test
[34]). These will be assessed at baseline and at 12 month follow-up.

Intervention exposure will be assessed by attendance at the exercise programme sessions. Web-tool usage will be assessed by number and duration of logins over the study period.

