#### Moderator and mediator analyses

To attempt to establish how the interventions work and for whom, we will conduct a series of mediation and moderation analyses following established bootstrapping procedures outlined in
[37]. Putative moderators will include participant demographic factors, baseline intentions to engage in activity, feelings of self-efficacy and autonomy.

Potential mediators will include number of implementation intentions formed (in web-tool arms), frequency and intensity of use of the web-based tool, enjoyment of the 12-week exercise programme, attendance at the programme, perceptions of autonomy over exercise during the training programme, and intentions to exercise post-exercise programme.

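### The primary ANCOVA is valid but names only baseline activity as covariate; adding other baseline values already collected would be a nearly free, modest gain in precision

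*Protocol article*

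**What the plan says.** Under Intervention effectiveness, the protocol article compares each intervention arm with control by t-tests and by a one-way analysis of covariance. Study arm is the factor, with "baseline activity scores as the covariate". No other covariate is named. Secondary outcomes are to be analysed in a similar way.

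Other baseline information is collected:

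- Measures: "Participants will complete the GPPAQ screening tool at the beginning and end of the study". Entry is limited to two GPPAQ classes, inactive and moderately inactive.
- Measures: because the IPAQ can overstate activity in sedentary people, "we will use a second validated self-report measure, the Self-Report Walking and Exercise Tables". The article does not say at which visits this second instrument is given.
- Sample description: age, sex, weight, height and BMI are recorded at screening and tabulated by arm.
- Moderator and mediator analyses: "Putative moderators will include participant demographic factors, baseline intentions to engage in activity, feelings of self-efficacy and autonomy".

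The sample size section assumes that "an effect size of 0.125 can be assumed for comparing means of MET-minutes per week and mmHg". For arms of 500 patients and a significance level of 5%, its claim is that "a power of 80% is obtained for a two-sided statistical contrast to show statistical significance". That calculation takes no credit for any covariate.

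**The concern.** A covariate that predicts the outcome takes variance out of the error term and narrows the confidence interval for the arm difference. The only covariate named here is self-reported activity, in a population for which the article itself doubts the main questionnaire. Restricting entry to less active people may also narrow the baseline range and weaken its correlation with activity a year later. Either would leave variance that a second activity measure, GPPAQ class, age, sex or intention might explain.

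The planned effect is small, so precision matters. With 2,000 patients, a handful of extra covariates costs almost nothing in degrees of freedom, and one that proves useless does essentially no harm. What is at stake is somewhat wider intervals than the collected data may require. Validity is not at stake.

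**Working it through.** **Inputs from the protocol article:** effect d = 0.125 SD; 500 per arm; two-sided 5%; 2,000 patients in four equal arms; baseline activity as the only named covariate.

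**Assumptions (the article gives none of these):** correlation ρ of baseline with 12-month activity, 0.3 to 0.7; share s of the remaining variance that added covariates explain, 2% to 10%; no dropout; d expressed in units of the unadjusted SD.

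**Step 1. The stated power.** For two arms of n each, power ≈ Φ(d·√(n/2) − 1.96).

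- 0.125 × √250 = 1.976, and Φ(0.016) = 50.7% (50.6% by the noncentral t).
- For 80% power, n = 2 × (1.96 + 0.8416)² / 0.125² ≈ 1,005 per arm.

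The stated 80% is therefore not reproduced with 500 per arm. Unadjusted, 500 per arm detects 0.177 SD with 80% power. To reach 80% at 0.125 SD, covariates would have to explain 1 − 500/1,004.6 ≈ 50% of the outcome variance, that is ρ ≈ 0.71.

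**Step 2. Adding covariates to the planned ANCOVA.** With R² = ρ² + s(1 − ρ²), power ≈ Φ(0.125 × √(250/(1 − R²)) − 1.96). Example at ρ = 0.5, s = 5%: R² = 0.25 + 0.05 × 0.75 = 0.2875; 0.125 × √(250/0.7125) = 2.341; Φ(0.381) = 64.9%.

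| ρ | baseline activity only | s = 2% | s = 5% | s = 10% |
|---|---|---|---|---|
| 0.3 | 54.5% | 55.3% | 56.6% | 58.9% |
| 0.5 | 62.6% | 63.5% | 64.9% | 67.2% |
| 0.7 | 79.0% | 79.8% | 81.0% | 83.1% |

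The gain runs from 0.8 to 4.6 points. The standard error is multiplied by √(1 − s): 0.990, 0.975 and 0.949, a fall of 1.0%, 2.5% and 5.1%. The required sample falls by s itself.

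For comparison, moving from the t-test to the ANCOVA already planned is worth 50.7% to 62.6% at ρ = 0.5. Most of the available gain is already in the plan if ρ is moderate.

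**Step 3. The second activity instrument alone.** Let r1 and r2 be the correlations of the two baseline measures with the 12-month score, and r12 their correlation with each other. Then R² = (r1² + r2² − 2·r1·r2·r12)/(1 − r12²), and the cut in residual variance is 1 − (1 − R²)/(1 − r1²). Assumed ranges: r1 0.3 to 0.5, r2 0.3 to 0.45, r12 0.4 to 0.55.

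| r1, r2, r12 | R² before | R² after | cut in residual variance |
|---|---|---|---|
| 0.50, 0.30, 0.55 | 0.250 | 0.251 | 0.1% |
| 0.45, 0.40, 0.55 | 0.203 | 0.236 | 4.2% |
| 0.50, 0.45, 0.50 | 0.250 | 0.303 | 7.1% |
| 0.40, 0.40, 0.40 | 0.160 | 0.229 | 8.2% |
| 0.30, 0.45, 0.40 | 0.090 | 0.220 | 14.2% |

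The first and last rows are the extremes over these ranges. At the favourable extreme, power goes from 54.5% to 60.9%; at the other it does not move. The gain depends almost wholly on correlations that nobody has stated.

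**The case against.** The strongest case against is that this is not an error at all. Adjusting for the outcome's own baseline is standard and usually captures most of what adjustment can give. A longer covariate list is often left to an analysis plan, which is not shown here. That stands as to weight. The point survives only because the article states a specific model that could be improved at almost no cost.

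Several stronger readings are tempting, and the document does not support them:

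- *That the article shows these values to be predictive.* It gives no correlation or R² for any of them. Demographics, intentions, self-efficacy and autonomy are listed as moderators, which concerns variation in treatment effect and not prognosis. For intention, the Background stresses that good intentions often fail. Plausible is as far as one can go.
- *That GPPAQ class must add much.* It has two levels over a restricted range.
- *That the second instrument is available as a covariate.* Its timing is not stated. The plural in "baseline activity scores as the covariate" also leaves open whether both instruments are meant.
- *That chance imbalance in age, sex or GPPAQ class biases the result.* After randomisation it does not, and the standard error allows for it.
- *That richer adjustment would rescue the power.* It would not, unless baseline activity alone already correlated at about 0.7 with the outcome.

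**Conclusion.** The point holds as a modest, nearly free improvement to a valid model. If the added covariates explain 2% to 10% of the variance left after baseline activity, the standard error falls by about 1% to 5% and power for one 500 against 500 contrast rises by about 1 to 5 points. For the second instrument alone, the cut in residual variance could be anything from 0.1% to 14% over the assumed correlations. All of this rests on assumed correlations and on no dropout.

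A reader might infer that the plan wastes a material amount of precision. The article contains nothing that would establish that. The gap between the stated 80% and the 50.7% obtained for the unadjusted comparison is a separate and much larger matter, which this change does not close.

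**What to change.** Name the covariates of the primary ANCOVA before unblinding: baseline IPAQ MET-minutes, GPPAQ class at entry, age, sex and baseline intention. Add the baseline Self-Report Walking and Exercise Tables score if that instrument is given at baseline, and state whether it is. For each secondary outcome, use that outcome's own baseline value with age and sex.

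Say also that the ANCOVA, rather than the unadjusted t-test, is the primary analysis. Both are listed and neither is named as primary, and the covariates help only in the former.

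The cost is a sentence or two in the analysis plan. No new data are needed for GPPAQ class, age, sex or baseline intention; for the second instrument this depends on its being given at baseline. The sample size statement needs its own correction and should not lean on this change.
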